## Abstract

Scientific evidence has shown that healthcare clowning can decrease the level of stress and anxiety in pediatric patients. However, little attention has been devoted to the potentially beneficial impact of clown visits in the child and adolescent psychiatry setting. Therefore, this pilot study aims at investigating short-term effects of clown visits by RED NOSES Clowndoctors Austria on stress and mood levels of children and adolescents in psychiatric care. The sample will consist of approximately 50 children and adolescents in inpatient psychiatric wards who receive clown visits on a weekly basis over four consecutive weeks. The examined intervention, i.e., the clown visits, is an integral part within the selected psychiatric institutions. Using a non-controlled pre-/post-test design, the level of salivary cortisol and self-reported stress and mood will be measured as primary outcomes before and immediately after each clown visit. Additionally, self-reported effects on care staff at the health care facilities will be assessed based on a questionnaire after each clown visit within the same time period of four weeks. Secondary outcome measures (i.e., health-related quality of life, emotional and conduct problems, perceived chronic stress) will be assessed at baseline and at close-out assessment after the four intervention weeks. Further control variables and potential moderators are included at baseline. Due to the nested data structure, multilevel modeling will be used to analyze the data. To our knowledge, this is the first study to examine the stress-reducing and mood-improving effects of clown visits on inpatients in child and adolescent psychiatry. Results will be relevant for the design of future large-scale RCTs and might provide valuable implications for the use of healthcare clowning to reduce stress and improve mood in children and adolescents in psychiatric care. The study is registered at ClinicalTrials.gov (Identifier: NCT04844398).

## Background

Hospitalized children often face a range of demanding experiences. Stress and anxiety are prevalent phenomena during hospital stays [1, 2]. Preoperative anxiety in pediatric patients is one of the primary outcomes investigated in previous research [3–5], although children report other problems as well; for example, hospitalized children often feel “alone, […] mad, and sad” [6]. Pain, loss of control, and disconnection from family and relatives can lead to physical and psychological impairments [7]. Even after discharge, children may exhibit symptoms of distress, such as restlessness and lower self-esteem [8]. In children in psychiatric care, stress and anxiety can be even more pronounced, as they might be part of the symptoms requiring inpatient treatment in the first place, and the process of adaptation to the context of hospitalization can exacerbate primary symptoms [9].

To address these issues and alleviate their impact on the patients’ well-being, humor interventions have been identified and used as an effective treatment in hospitals for decades [10, 11]. Most commonly, these take the form of professional hospital clowns and are either carried out in independent visits or integrated into hospital routines. In Austria, such interactive clown performances are offered, inter alia, by RED NOSES Clowndoctors Austria, which is part of RED NOSES International (RNI), a non-profit association providing professional clown programs in the medical and social care settings. RNI identifies three target areas of healthcare clowning for clinical patients stemming from common problems associated with hospitalization: (a) Social disconnection: patients may be separated from family and friends for a prolonged period of time, resulting in feelings of loneliness and exclusion; (b) Painful emotions: patients may experience heightened levels of stress, fear, and anxiety; (c) Challenging environments: hospital environments may be unable to provide adequate psychosocial support, leading to feelings of boredom and powerlessness [12]. Healthcare clowning aims at addressing these issues by offering individual attention to patients in need, switching focus away from negative emotions to humorous play, and valuing a patient’s unique strengths in an otherwise possibly impersonal environment. These encounters lead to improved communication, attention, energy, and mood [13]. Moreover, healthcare clowning has been conceptualized as a model for a more self-compassionate way of dealing with one’s own shortcomings and hardships [14]. Presumably, a particularly suitable target group for the clowning approach are children and adolescents, who might respond especially well to clowning due to the immediate, non-intellectual approach [14]. Clown interventions in hospital settings are therefore assumed to be highly effective among pediatric inpatients.

Previous research on the effectiveness of healthcare clowning has mainly focused on interactive clown performances for children and adolescents in intensive care or undergoing medical surgery. Specifically, clown visits have been shown to reduce preoperative anxiety [15, 16] and stress [17], salivary cortisol [18], pain during medical procedures [19, 20], and the need for sedation [21] in pediatric patients. With the exception of a few pilot studies with adult patients [22–24], little attention has been paid to potential benefits of clowns in the psychiatric setting. For adult patients in a closed psychiatric ward, an interactive clown performance during a period of bi-weekly clown visits led to reduced disruptive behaviors, including less agitation, aggression, and self-injury [24]. To our knowledge, there is no prior study that has investigated the impact of clown visits in the setting of child and adolescent psychiatry. Hence, the current pilot study aims at addressing this gap.

A small number of studies have demonstrated positive effects not only for patients, but for medical staff as well. Anesthetists appreciated the presence of clowns accompanying their medical rounds [25], and professionals performing venipuncture benefitted from less anxiously agitated patients when assisted by clowns [26]. Most prominently, strong effects were observed on nursing staff, where clown interventions have been shown to improve nurse-patient interactions [27, 28] as well as professional communication throughout their workday [28]. Ghaffari et al. [29] found that humor enhanced nurses’ mental and emotional well-being; the authors further highlighted its ability to promote an energetic and creative state for nurses in clinical settings as well as help them to overcome sadness and despair [30]. This finding was supported by other studies reporting reduced negative mood in nurses experiencing the clown performances [28]. In a pilot study, Wild et al. [31] described pediatric psychiatric care staff reports about the helpfulness of healthcare clowning in their daily routine and their expressed support to continue the program—a finding that other scholars have reported similarly [28, 32].

### Study aims and hypotheses

To our knowledge, this pilot study is the first to investigate the impact of clown visits on stress and mood of children and adolescents in inpatient psychiatric care, examining patients’ salivary cortisol in addition to self- and staff-reports on stress and mood perception. A second novelty is that we assess effects on stress and mood over the course of multiple visits, allowing for insight into dose-response relationships. We expect that children and adolescents involved in an interaction with the clowns will experience a decrease in their subjective and physiological stress levels as well as improved mood by redirecting their attention to the current pleasurable moment. Specifically, we hypothesize that (1) children and adolescents will report less perceived stress and improved mood and that (2) they will display a reduced cortisol level after the experience of a clown visit compared to before. We further expect that (3) the more frequently children and adolescents experience the weekly clown visits over the course of the four-week intervention, the stronger the stress-reducing and mood-improving effects will be. Last, we assume that (4) perceptions of care staff will indicate positive effects of the clown visits on their own individual mood, the atmosphere within the staff team, and the patients’ well-being.

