## Materials and methods

### Participants

This pilot study will be conducted with children and adolescents of any gender and psychiatric diagnoses who currently are inpatients in Austrian child and adolescent psychiatric institutions cooperating with RED NOSES Clowndoctors Austria. Specific inclusion criteria are (1) being aged between 7 and 18 years and (2) regular participation in clown visits at the relevant health care facility on a weekly basis. Exclusion criteria are (1) potential negative impacts of clown visits or study participation on participants’ mood or well-being according to medical or paramedical care staff of the relevant health care facility and (2) insufficient command of German (for self-administered questionnaires only).

Participants will be recruited from two cooperating psychiatric healthcare facilities in Austria. The visits will take place in at least two different wards of each participating psychiatric care facility. In each ward, a maximum of 10 participants will be targeted. The four-week intervention assessments will take place twice in both clinics with different patients (time interval of approximately four to seven weeks between the two assessment phases). The first recruitment phase is initiated by a staff member of RED NOSES Clowndoctors, who regularly visits those clinics. Within the clinics, the recruitment process will be assisted by the care staff of the relevant wards. After being informed about the study goals and data collection process, care staff will evaluate the eligibility of specific patients regarding potential negative impacts of clown visits or study participation. If there are no anticipated negative consequences on participants’ health or well-being, informed consent will be obtained from participants and, in case of underage participants, their parents or legal guardians prior to the start of data collection.

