### Intervention

Clown visits will be carried out routinely by two professional clown artists from RED NOSES Clowndoctors Austria once a week for four consecutive weeks either in a group setting or an individual setting. The selection of artists, type of setting (group or individual), duration of clown visits, and specific artistic sequences will correspond to usual clown visits in those institutions, following internally organized routines instead of being standardized. The essence of the clown visit is to catch the patient’s attention proactively and reach the highest possible level of engagement. The specific artistic sequences and type of setting are implemented spontaneously according to the situational atmosphere and current condition of participants. One clown visit in the group setting will last between 1 and 2 hours including individual as well as collective attention depending on age, number of participants, and situational atmosphere. In the individual setting, each participant will be engaged individually between 5 and 20 minutes by the clown, depending on the situational mood and condition of the patients. The clown artists are not involved in any study-related research activities.

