#### Sociodemographic and clinical data and control variables for salivary cortisol (children and adolescents)

A self-administered questionnaire to assess children’s and adolescents’ sociodemographic data includes information about gender, age, type of school attended before psychiatric admission, first language, and number of previously experienced clown visits. Further, psychiatric diagnoses or reasons for treatment, admission date at the clinic, number of previous clinic stays, current treatment (forms of therapy), current medication, attending in-house clinic schooling, and somatic comorbidities are assessed by a self-administered questionnaire filled out by care staff. Control variables for salivary cortisol are measured by a self-administered questionnaire completed by children and adolescents (i.e., intake of food, chewing gums, or relevant drinks (i.e., coffee, tea, cola, juices, and alcohol); tooth brushing or smoking within an hour before the collection of the saliva samples; whether they did sport in the last 48 hours; whether they took medication on the same day; and whether they feel healthy).

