### Statistical analysis

Due to the nested data structure (outcomes being nested within time points and in turn nested within participants), change in primary outcome measures (i.e., perceived stress and mood, salivary cortisol) will be analyzed by means of multilevel modeling using R packages (e.g., lme4 package [58]) to disentangle within-subject and between-subject variance. Level 1 comprises variables that are assessed repeatedly (i.e., the primary outcomes assessed before as well as immediately after each of the four clown visits), whereas level 2 specifies time points. Level 3 comprises of individual participants. Note that to prevent convergence issues, the best-fit model out of the following models will be used to test hypotheses: Fixed slope, random intercept for level 2 and 3 (Model 1); random slope at level 3 (Model 2); random slope at level 2 (Model 3); random slope at levels 2 and 3 (Model 4).

Given the complexity of the models, further analyses are to be considered exploratory in view of the small sample size of this pilot study. Potential moderator effects (number of visits, enjoyment, baseline variables) will be examined by testing cross-level interactions, provided the best-fit model allows for these analyses.

Missing data will be handled with full-information maximum likelihood (FIML) estimation, which uses all available information in the variance/covariance matrix to compute model parameters and produces less biased estimates than listwise or pairwise deletion or mean substitution [59]. Statistical significance will be assumed at α ≤ .05, as conventional. To reduce the chance of false discovery, alpha error correction will be applied using the Benjamini-Hochberg procedure [60].

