There are several strengths of this study. We will assess children’s and adolescents’ stress levels by subjective (self-report) as well as physiological measures (salivary cortisol), which enables us to measure the immediate effect on stress on two different levels, enhancing the validity of assessments. The inclusion of secondary outcomes provides further insights of the overall impact of the four-week intervention. As staff reports are collected as well, conclusions can be drawn from various perspectives. Experiences of care staff have only been included in a limited number of studies so far. More attention to this area is needed, as those few studies found positive effects of healthcare clowning on care staff and their working conditions in psychiatric settings [28, 31, 32]. Additionally, control and moderator variables are assessed. Thereby, we will be able to account for statistical controls as well as to identify potential subgroups benefiting most from interventions. Moreover, the repeated measures design (i.e., one clown visit on a weekly basis over four consecutive weeks) allows the investigation of cumulative effects as a result of repeated clown visits.

Although this pilot study aims at closing an important research gap, we are also aware of its limitations. First, the lack of an untreated control group will preclude causal inferences. Thus, there is a chance that alternative explanations such as other temporal developments could account for found effects rather than the intervention per se. However, as assessments take place before and after each clown visit, within-subject temporal trends can still be examined. Second, due to the target sample size of approximately 50 children and adolescents and the circumstance that the study only takes place in two facilities, generalizability of study results is inherently limited. Third, not all questionnaires used in this study have been validated in previous research. We must therefore first examine whether the instruments in question, which were developed on the basis of theoretical considerations, also prove themselves empirically.

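### Hypothesis 3 and the Discussion claim dose-response and cumulative effects, but in this one-arm weekly design visit number cannot be separated from time in treatment

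*Protocol article*

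**What the plan says.** Under *Study aims and hypotheses*, the protocol article names repeated assessment as a novelty of the study, "allowing for insight into dose-response relationships". Hypothesis 3 then states that "the more frequently children and adolescents experience the weekly clown visits over the course of the four-week intervention, the stronger the stress-reducing" effect, and likewise for mood. It stands beside hypotheses 1 and 2 without qualification. The Discussion lists among the strengths that the repeated-measures design "allows the investigation of cumulative effects as a result of repeated clown visits".

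The design sections read differently. *Trial design* describes a single arm, with no controls and no planned differences in the intervention. *Intervention* has the visits take place "once a week for four consecutive weeks". The Abstract says that the intervention "is an integral part within the selected psychiatric institutions", and the baseline questionnaire asks for the "number of previously experienced clown visits". Care staff report the admission date.

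The only apparent test of hypothesis 3 is in *Statistical analysis*: "Potential moderator effects (number of visits, enjoyment, baseline variables) will be examined by testing cross-level interactions". It is exploratory and depends on what the best-fitting model allows.

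**The concern.** A dose-response statement needs dose to vary in some way that is not simply the passage of time. Here everyone follows the same weekly schedule while under inpatient care. As the visits go on, the child has also been treated for longer, has grown used to the ward, and has completed the same scales and saliva collection more often. Study visit 1 also need not be the first exposure, because clown visits are already routine in these clinics.

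If the pre/post change grows from visit 1 to visit 4, the article's wording invites the reader to see a dose effect. The pilot is meant to inform later randomised trials, so a time trend could be carried forward as evidence that more visits work better.

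**Working it through.** **The plan's own figures.** The article gives no figure for hypothesis 3. Its minimum of about 30 participants refers to a paired pre/post comparison. It is reproduced by a one-tailed paired t-test with d = 2f: the smallest effect, f = .23, gives d = .46 and n = 31. It has no bearing on this point.

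**Step 1: what a within-child trend identifies.** For child i at study visit k (k = 1 to 4, all attended), let P be the clown visits before the study and T the weeks from admission to study visit 1. Then:

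- total visits so far = P + k
- weeks since admission = T + (k − 1)
- number of pre/post testings = k

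Suppose the pre/post change depends linearly on these three with coefficients b1 (dose), b2 (time) and b3 (testing). The change then equals a constant for the child plus (b1 + b2 + b3) × k. Only the sum of the three coefficients can be estimated from the child's trend. Missed visits do not help to separate dose from testing, because each attended visit brings one pair of measurements.

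**Step 2: how far missed visits separate dose from time.** The article gives neither attendance nor time from admission to first study visit, so both are assumed. The simulation used 50 children, four weekly visits, visits missed at random and 300 repeats. The within-child correlation between cumulative study visits and time since admission was:

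| Attendance (assumed) | Within-child r |
|---|---|
| 100% | 1.00 |
| 90% | 0.99 |
| 75% | 0.97 |

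Even at 75% attendance the two share 0.97² = 0.94 of their variance.

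**Step 3: the other reading, visits attended compared between children.** With four scheduled visits and independent attendance probability p, the SD of visits attended is √(4p(1 − p)), and 50p⁴ of 50 children attend all four.

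| p (assumed) | SD of visits attended | Attend all four, of 50 |
|---|---|---|
| 1.00 | 0 | 50 |
| 0.95 | 0.44 | 40.7 |
| 0.90 | √0.36 = 0.60 | 32.8 |
| 0.80 | √0.64 = 0.80 | 20.5 |
| 0.70 | √0.84 = 0.92 | 12.0 |

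With high attendance there is little contrast. With lower attendance there is more, but it is not randomised.

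**Step 4: does adding earlier visits rescue the claim?** P does not change within a child, so centring total visits on the child's mean gives (P + k) − (P + mean k) = k − mean k, the visit index again. Across children, total visits including earlier ones stay tied to time since admission. In the same simulation, with mean prior stays of 0.5 to 8 weeks assumed, r was 0.98 to 1.00 at full attendance and 0.83 to 0.98 at 75%. Counting earlier visits describes exposure better but does not separate it from time.

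**The case against.** The strongest reply is that the article already makes the necessary reservations. The moderator analyses are labelled exploratory. The Discussion concedes that causal conclusions are not possible without a control group and that other developments over time could explain the findings. Earlier visits and admission date are collected, and baseline variables are listed as moderators. Each outcome is measured before and after each visit, so a slow recovery shared by both readings cancels from the change. How the number of visits is coded is ordinary detail for an analysis plan that is not shown.

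Much of this stands. The coding is not a fault, and time matters here only if it alters the acute response. But that is exactly what hypothesis 3 concerns, so cancelling the shared trend does not help. The general concession also leaves the specific dose-response and cumulative-effect claims in place.

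Several stronger readings are tempting and are not supported:

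- **That participants must already be regular attenders.** The criterion is "regular participation in clown visits at the relevant health care facility on a weekly basis". It does not say whether this means before or during the study.
- **That attendance reflects recovery through discharge.** The article gives no discharge rates, lengths of stay or reasons for missed visits.
- **That leaving out earlier visits dilutes the within-child trend.** Earlier visits are a constant for each child and drop out of a linear within-child slope. Hypothesis 3 is also limited to the four study weeks.
- **That visit number and time in hospital are collinear throughout.** This holds within children. Pooled over children at full attendance, the simulated r falls from 0.92 to 0.15 as the assumed mean prior stay rises from 0.5 to 8 weeks.

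**Conclusion.** The point holds as one about inference. The article ascribes to the design an ability to show dose-response and cumulative effects that a single arm on a common weekly schedule does not have. Within a child the confounding with elapsed time is complete at full attendance and nearly complete (r about 0.97) at 75%. Between children the SD of visits attended is 0.60 or less at 90% attendance or above. The algebra rests only on the weekly schedule and an assumed linear effect. The attendance and prior-stay figures are assumptions that show the range.

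The pre/post comparisons in hypotheses 1 and 2 are not touched by this point. The claims should be narrowed; the data collection need not change.

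**What to change.** 1. In *Study aims and hypotheses* (the novelty statement and hypothesis 3) and in the strengths paragraph of the Discussion, replace the dose-response and cumulative-effect claims with: *trend in the pre/post change across visits, not separable from time in treatment*.
2. Test that trend as the interaction of pre/post with visit order.
3. Enter the number of previous clown visits and the days from admission to the first study visit as between-child moderators of the pre/post change. Report them as exploratory, and say that they are not a means of separating dose from time.

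The cost is wording and a short specification. Previous visits and admission date come from the baseline questionnaires, and the visit date comes from the examiners' form, so nothing new is collected. The downside is that hypothesis 3 will support a weaker conclusion.
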